### Recruitment

2.9

Patients from the Balearic Islands who experienced a TRD episode will be recruited through cooperation with mental health workers and applications will be submitted via social media. To ensure the patients meet the inclusion criteria, the assessors will administer the MINI questionnaire by telephone, as with all the other tests.^[37]^ If a participant is eligible, the researcher will administer the baseline questionnaire. Recruitment and baseline assessments will be performed until the sample size is 180. All collected information will be processed as stipulated in current legislation regarding the protection of personal data.

### Assignment of interventions

2.10

Eligible patients will be randomized once they agree to participate and provide written informed consent. After the enrolment visit, each patient will be randomly assigned to the MBCT Intervention, Lifestyles Intervention or Placebo group in a 1:1:1 ratio. Randomization will be performed using a computer-generated random assignment sequence with a block randomization method and Random Allocation software (v.2.0). A hospital unit unrelated to this clinical trial will perform the randomization of patients to the different study groups.

### Statistical analyses

2.11

All researchers conducting the data analysis will be blinded to group allocations. All eligible randomized patients who were evaluated at least once using the efficacy indicators will be defined as the “full analysis set”; all eligible randomized patients who attend at least 80% of the scheduled sessions will be defined as the “per-protocol set.” The effectiveness measurements will be evaluated mainly by intention-to-treat analysis using the full analysis set and supplemented by per-protocol analysis.

Numerical variables with normal distributions will be presented as means ± standard deviations, and categorical variables as absolute and relative frequencies. Numerical variables with skewed distributions will be presented as medians, minima, and maxima. Analysis of variance will be used to compare the 3 groups at multiple time points. In the main analysis, missing data will be replaced using multiple imputation. Complete-case analysis will be also conducted as a sensitivity analysis to assess the robustness of results from the multiple imputation procedure. Hypothesis testing will be performed using a 2-sided test and presented with 95% confidence intervals. A *P* value less than .05 will indicate statistical significance. All analyses will be performed using SPSS version 21.0 and STATA version 16.1.

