### Intervention

2.5

Patients will be randomly allocated to 1 of 3 groups:

1.Intervention group: Treatment prescribed by the mental health team, written suggestions for lifestyle changes, and an 8-week lifestyle change promotion program.2.Placebo-control group: Treatment prescribed by the mental health team and written suggestions for lifestyle changes.3.Active-control group: Treatment prescribed by the mental health team, written suggestions for lifestyle changes, and an 8-week iMBCT program.

The eight 3-hour group sessions administered to the intervention group (Table 1) will include review and assignment of homework on the following topics about depression and healthy lifestyles: symptoms, causes, course, and treatment of depression; importance of physical exercise for physical and mental health; how to exercise safely and comfortably; motivation to incorporate physical exercise into daily routines; importance of good nutrition for improving physical and mental health, and healthy eating guidelines; importance of a social support network, with practical proposals for improvements; sleep-wake rhythm and sleep hygiene, with practical proposals for improvement; need for appropriate exposure to sunlight, with practical recommendations; role of negative ruminations in maintaining depression, with strategies to detect and stop this behavior; contact with nature, with practical recommendations for improvements. All strategies will be reviewed and there will be a final opportunity to recommend their combined long-term use.

**Table 1 T1:** Sessions descriptions for the intervention group and the active control group.

	Lifestyle change sessions (intervention group)		Mindfulness-based cognitive therapy sessions (active control group)	
		
Session	Topic	Homework	Topic	Homework

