8	Review of all strategies and a final opportunity to recommend their combined long-term use.	Proposals for maintaining all these strategies in the future.	Plan a future by living mindfully.	Proposals for maintaining all these strategies in the future.

The eight 3-hour group sessions administered to the active control group (Table 1) will review an assignment of homework on the following topics about depression and mindfulness: symptoms, causes, course, and treatment of depression; concept of full attention; changing from living on “automatic pilot” to living consciously and deliberately; observations of breathing and the body; changing the form of relating to experiences through thought to feeling them directly; labeling different experiences (pleasant, unpleasant); changing from delving into the past and anticipating the future to being fully present in the moment; changing from trying to avoid, escape, or eliminate unpleasant experiences to approaching them with curiosity and interest; changing from needing things to be different to simply letting them be as they are; changing from considering thoughts as true and real to considering them as mental processes that may not correspond to reality; changing from treating yourself harshly to caring for yourself with affection and compassion; planning a future by living mindfully.

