## Discussion

3

Mental health professionals have the responsibility to adapt their health care interventions to health emergency situations, such as the current COVID-19 pandemic, and must continue to offer demonstrably useful therapeutic alternatives to their patients. Patients with TRD are among the neediest in these circumstances, because provision of face-to-face care is very difficult. This study will examine the effect of an intervention that attempts to help patients with TRD to modify their lifestyles by using information and communications technologies (ICTs) and videoconferencing instead of traditional face-to-face interactions. To assess the efficacy of lifestyle modification, we will compare this intervention group with 2 control groups: a placebo control group, which will receive minimal assistance (written recommendations for a healthy lifestyle), and an active control group, which will participate in an iMBCT program.

The time commitment is the same for the active control (iMBCT) group and the intervention (lifestyle program) group, and iMBCT has been used successfully for patients with TRD in face-to-face settings. We hypothesize that at the end of the 12-month follow-up, the lifestyle program group will show greater adherence to the intervention and will therefore experience greater improvement than the other 2 groups. If this Internet-based multimodal lifestyle intervention program is useful as an adjunct to the pharmacological treatment of depression, this approach should be considered for the management of patients with TRD in similar emergency situations.

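### The per-protocol set is defined by session attendance and so cannot be applied to the placebo-control arm; the full analysis set leaves open whether it covers all randomised patients

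*Protocol article*

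**What the plan says.** Section 2.11 (Statistical analyses) defines two analysis sets.

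- **Full analysis set:** "All eligible randomized patients who were evaluated at least once using the efficacy indicators will be defined as the" full analysis set.
- **Per-protocol set:** "all eligible randomized patients who attend at least 80% of the scheduled sessions will be defined as the" per-protocol set.

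Effectiveness is to be "evaluated mainly by intention-to-treat analysis using the full analysis set and supplemented by per-protocol analysis". The same section adds: "In the main analysis, missing data will be replaced using multiple imputation".

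Section 2.5 (Intervention) describes sessions for two arms: "The eight 3-hour group sessions administered to the intervention group" and "The eight 3-hour group sessions administered to the active control group". The third arm is described as follows: "Placebo-control group: Treatment prescribed by the mental health team and written suggestions for lifestyle changes". The Discussion repeats this, calling it "a placebo control group, which will receive minimal assistance (written recommendations for a healthy lifestyle". No other adherence rule is given for that arm.

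On timing, Table 2 places a BDI-II one week before allocation, and section 2.9 has the baseline questionnaire given once a participant is found eligible.

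**The concern.** A per-protocol rule has to be something that a patient in every compared arm can meet or fail. This one is stated for all randomised patients, yet a third of them have nothing to attend. Whoever programmes the analysis must choose between leaving the arm out and letting everyone in it through, and the two choices answer different questions. The second sets patients who completed nearly all of a demanding programme against everyone in the control arm, so better motivated or less ill patients could look like a treatment effect.

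The trial's own reasoning sharpens this. The Discussion predicts greater adherence in the lifestyle arm and attributes greater improvement to it. Adherence is thus a post-randomisation variable expected both to differ between arms and to be related to outcome.

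The second issue is the main analysis population. If being evaluated at least once means after baseline, patients who leave early drop out of an analysis called intention-to-treat. They would do so after an allocation that, as the Discussion acknowledges, cannot be blinded to participants, and although multiple imputation is already planned.

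**Working it through.** **The plan's own figures.** The article gives no expected size for either analysis set. The denominators come from section 2.8: difference 6 points, SD 9.8, two-sided alpha 0.05, power 0.85. Then n = 2 × [9.8 × (1.960 + 1.036) / 6]² = 47.9, so 48 per group, and 48 × 1.25 = 60 reproduces the stated 60 per group (180 in total). This only fixes the denominators used below.

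**The attendance threshold.** 0.80 × 8 = 6.4. Six sessions is 75% and fails; seven is 87.5% and passes. The rule is therefore at least 7 of 8.

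**Applying it to each arm.**

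| Arm | Scheduled sessions | Can the rule be applied? |
|---|---|---|
| Lifestyle | 8 | Yes |
| iMBCT | 8 | Yes |
| Placebo-control | 0 | No (0 of 0) |

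- Reading A, no placebo-control patient qualifies: the pool falls from 180 to at most 120 and there is no per-protocol contrast with placebo-control.
- Reading B, all placebo-control patients qualify by default: up to 60 unselected controls are compared with selected attenders.

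**Size of the selection effect under reading B, with no true treatment effect.** Assumptions, none from the documents: a proportion p of 0.6 to 0.8 meets the threshold; the latent tendency to attend has correlation ρ of 0.1 to 0.4 with a better BDI-II; both are normal. The SD of 9.8 is from section 2.8. The attenders' mean shifts by ρ × 9.8 × φ(z)/p, where φ is the normal density at the cut-off that leaves a proportion p above it. The factor φ(z)/p is 0.644, 0.497 and 0.350 for p = 0.6, 0.7 and 0.8.

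| p | ρ = 0.1 | ρ = 0.2 | ρ = 0.3 | ρ = 0.4 |
|---|---|---|---|---|
| 0.6 | 0.63 | 1.26 | 1.89 | 2.52 |
| 0.7 | 0.49 | 0.97 | 1.46 | 1.95 |
| 0.8 | 0.34 | 0.69 | 1.03 | 1.37 |

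The range is 0.34 to 2.52 points. As a share of the target, 0.34/6 = 6% and 2.52/6 = 42%.

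The chance of a false positive follows from comparing 60p attenders with 60 controls, with standard error 9.8 × √(1/(60p) + 1/60). At p = 0.8 and ρ = 0.1 the standard error is 1.90 and the two-sided error is about 5.4%. At p = 0.6 and ρ = 0.4 they are 2.07 and about 23%. The nominal level is 5%.

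**The full analysis set.** Two readings fit the wording.

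- If the pre-allocation BDI-II counts, every properly enrolled patient has been evaluated once, and the set equals all randomised patients.
- If only post-baseline evaluations count, patients with none are excluded. Section 2.8 allows at most 25% dropout, so at most 0.25 × 60 = 15 per arm. That ceiling is reached only if every dropout occurs before the week-8 assessment. The article does not say when dropout is expected.

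**The case against.** The strongest reply is that the consequence is small. The per-protocol analysis is supplementary, and arm-specific adherence rules are often left to a fuller document. The first part stands and limits the weight of the point. The second does not: the article states a rule for all randomised patients, and it is that stated rule which cannot be applied to one arm.

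The selection figures rest on assumed attendance and correlation, and the direction (attenders doing better) is assumed too. That is correct, which is why a range is shown. The structural fault does not depend on them.

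A reader might infer three stronger things that the article does not support.

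- *That the full analysis set is narrower than intention-to-treat.* Section 2.11 does not say post-baseline, BDI-II is taken before allocation, and section 2.10 randomises only eligible patients. The inclusive reading is at least as natural and fits the planned imputation. Only ambiguity is established.
- *That 15 of 60 patients per arm would be lost from the main analysis.* This is a ceiling on one of two readings; a patient who leaves after week 8 stays in the set.
- *That the fault hits the main contrast.* The Introduction states the hypothesis against both control groups and ranks neither first. For lifestyle versus iMBCT the set is well defined.

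A further objection concerns a tempting repair: a complier-average effect with compliance set at 7 of 8 sessions. It assumes no benefit from attending one to six sessions, up to 6 × 3 = 18 hours of an active programme. That is implausible and would tend to inflate the estimate. This objection stands and shapes the fix.

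**Conclusion.** The point holds for the per-protocol set: its only criterion has no meaning in the placebo-control arm, so the contrast with that arm is either unavailable or open to selection bias. If the arm is kept whole, the bias could plausibly be about 0.3 to 2.5 BDI-II points. This is conditional on the assumed attendance and correlation, and on attenders tending to have better outcomes.

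For the full analysis set, the finding is an ambiguity to close, with an unknown and possibly zero number of patients affected. The plan should be changed on both counts. The main analysis does not rest on the per-protocol set, so the trial's primary conclusion is not threatened by that part.

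**What to change.** 1. **Per-protocol set.** Limit the attendance-based set to lifestyle versus iMBCT and label it descriptive, because even there it conditions on attendance after randomisation.
2. **Contrasts with placebo-control.** Either drop the per-protocol analysis, or replace it with a complier-average estimate using randomisation as the instrument. Define compliance as attending any session, or use the number of sessions attended as a dose. State the exclusion restriction: with the any-session definition, allocation has no effect on those who attend none. Use the 7-of-8 cut only as a sensitivity analysis.
3. **Full analysis set.** Define it as all randomised patients, analysed as allocated, with the multiple imputation already planned for missing outcomes.

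The cost is a change of wording and, if the complier-average estimate is chosen, one additional model with a wider interval than the per-protocol comparison. The attendance records it needs are those the present rule already requires.

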In addition to investigating the effect of modification of individual lifestyle factors, there has been progress in studying modification of combinations of lifestyle factors as a therapeutic tool for various medical conditions and mental disorders, such as depression.^[17–20]^ We recently tested a multimodal program that includes interventions that are particularly effective for patients with depression: daily physical activity, adherence to a Mediterranean diet, sleep hygiene, and regulated exposure to sunlight.^[21]^ Other studies also examined the effect of other interventions, such as promoting sociability and teaching emotional self-control techniques, that should also be considered.^[22,23]^ Some researchers proposed this approach as an alternative to psychotherapy or pharmacotherapy as the first treatment for depression.^[9]^ There is evidence that the clinical manifestations of depression decreased at 2 to 6 months after patients followed specific recommendations regarding improvements to lifestyle.^[9]^ However, this benefit subsequently disappeared, probably because of the limited duration of support, monitoring, and supervision.^[22]^ Group therapy has the potential to promote long-term adherence to an intervention program and improve patient outcome.^[24]^

Extensive scientific evidence indicates that online treatments for affective disorders are effective.^[25]^ The benefits of these treatments, compared with usual treatments, show a clear need to consider this approach in treatment guidelines for depression, regardless of symptom severity.^[26]^ Online treatments and teletherapy could therefore be a cost-effective alternative to traditional psychological care for the prevention of relapses and depressive episodes.^[27]^ The “Smile is Fun” program is an example of an effective online intervention that helped patients with moderate symptoms of stress and depression.^[27]^

Previous research of online psychological treatments mainly focused on Internet-based cognitive behavioral therapy (iCBT), and found that this was an effective and practical alternative to face-to-face interventions for treatment of depression.^[28]^ Some studies also demonstrated the effect of practicing mindfulness as an online treatment for depression.^[27]^ Moreover, a recent study reported that the combination of practicing mindfulness and iCBT (iMBCT) had potential for treatment of depression.^[29]^

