### Sample size

2.8

Scientific evidence suggests that a 17% reduction in the BDI-II score^[38]^ is clinically relevant.^[64]^ A previous study by our team that examined psychiatric outpatients indicated the average BDI-III score at the beginning of the study was 24.5 (SD = 9.8).^[9]^ Thus, we considered a reduction of 6 points or more to indicate a clinically significant benefit. We estimate a maximum dropout rate of 25%. Accepting an α risk of 0.05 and a β risk of 0.15 in a bilateral contrast, 60 subjects will be required for each group. Thus, the total sample size will be 180.

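### Two of the three arms are treated in groups, but the named ANOVA and the sample size make no allowance for correlation within therapy groups

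*Protocol article*

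**What the plan says.** Section 2.5 (Intervention) describes both programmes as group-delivered: "The eight 3-hour group sessions administered to the intervention group" and, in parallel, "The eight 3-hour group sessions administered to the active control group". The third arm has no sessions: "Placebo-control group: Treatment prescribed by the mental health team and written suggestions for lifestyle changes". Section 2.10 (Assignment of interventions) randomizes individuals: "each patient will be randomly assigned to the MBCT Intervention, Lifestyles Intervention or Placebo group in a 1:1:1 ratio".

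Section 2.11 (Statistical analyses) names one method for the comparison: "Analysis of variance will be used to compare the 3 groups at multiple time points". The groups in that sentence are the trial arms. No therapy-group or therapist term is mentioned. Missing data are to be multiply imputed, again with no reference to therapy group.

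Section 2.8 (Sample size) starts from a BDI-II "score at the beginning of the study was 24.5 (SD = 9.8") and a target difference: "we considered a reduction of 6 points or more to indicate a clinically significant benefit". With a two-sided alpha of 0.05, beta of 0.15 and up to 25% dropout it arrives at 60 per arm and 180 in total. It gives no therapy-group size, ICC or design effect.

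**The concern.** Patients in two arms spend eight sessions of three hours, 24 hours in all, with the same small set of peers. Outcomes of people treated together may be more alike than those of people treated apart. If so, each therapy group carries less information than the same number of independent patients. An ordinary ANOVA, which assumes independent errors with one common variance, then understates the standard error.

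The problem is uneven across the arms. Both sides of lifestyle versus iMBCT are clustered, but only one side of lifestyle versus placebo-control is. The hypothesis in the Introduction is superiority over both controls, so both contrasts are affected. What is at stake is a false-positive rate above the stated 5%, confidence intervals that cover less than 95%, and less real power than section 2.8 claims.

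**Working it through.** **Inputs from the article:** difference 6, SD 9.8, two-sided alpha 0.05, power 85%, dropout 25%, 60 per arm.

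**Assumptions (not in the article):** groups of m = 10 at the start and ICC from 0.01 to 0.10. If dropout is spread evenly, 10 x 0.75 = 7.5 patients per group are observed.

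**Step 1: reproduce the stated size.** n = 2 x [9.8 x (1.960 + 1.036) / 6]² = 47.9, rounded up to 48 evaluable per arm. Then 48 x 1.25 = 60, exactly the stated figure. No design effect is hidden in it. (Dividing by 0.75 would give 64. That is a separate matter. It is why power at 45 completers is below 85% even without clustering.)

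**Step 2: variance multiplier V.** The design effect is DE = 1 + (m - 1) x ICC.
- Lifestyle versus iMBCT (both arms clustered): V = DE.
- Lifestyle versus placebo-control (one arm clustered): V = (1 + DE) / 2.

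**Step 3: actual type I error of the unadjusted 5% test** = 2 x [1 - Phi(1.96 / sqrt(V))].

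**Step 4: power with the correct standard error,** at 60 x 0.75 = 45 per arm: Phi(6 / [9.8 x sqrt(2V/45)] - 1.96). With V = 1 this is Phi(6/2.066 - 1.96) = 82.7%.

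Results with 7.5 observed per group:

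| ICC | DE | Type I, vs iMBCT | Type I, vs placebo-control | Power, vs iMBCT | Power, vs placebo-control |
|---|---|---|---|---|---|
| 0 | 1.000 | 5.0% | 5.0% | 82.7% | 82.7% |
| 0.01 | 1.065 | 5.8% | 5.4% | 80.3% | 81.5% |
| 0.02 | 1.130 | 6.5% | 5.8% | 78.0% | 80.3% |
| 0.05 | 1.325 | 8.9% | 6.9% | 71.3% | 76.8% |
| 0.10 | 1.650 | 12.7% | 8.9% | 61.8% | 71.3% |

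Using the t distribution instead of the normal lowers each power by about one point: 81.9% without clustering, then 79.5% to 60.9% versus iMBCT and 80.7% to 70.4% versus placebo-control.

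If all 10 patients per group are observed and the ICC is 0.10, DE = 1.90 and type I error reaches 15.5% and 10.4%.

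**Step 5: simulation check** with 60 per arm, groups of 10 and 40,000 replicates. The three-arm F test rejects in 5.1% of trials at ICC 0, 5.9% at 0.01, 6.8% at 0.02, 10.0% at 0.05 and 15.7% at 0.10. At ICC 0.10 the pairwise tests reject in 15.8% (versus iMBCT) and 10.6% (versus placebo-control). The formulas with m = 10 agree.

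**The case against.** Several points on the other side are sound and limit the claim.

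- A reader might infer that type I error does exceed 5%. The article does not establish that. The inflation requires a positive within-group correlation. At an ICC of 0 there is none, and at 0.01 it is under one percentage point.
- A reader might take the Introduction's sentence "Group therapy has the potential to promote long-term adherence to an intervention program and improve patient outcome" as the authors' own admission of correlated outcomes. It speaks of the average benefit of the group format. A benefit that is equal in every group produces no correlation, so the sentence is not evidence of variation between groups.
- A reader might assume a shared therapist within each group, or one per arm. The article does not say who leads the sessions. Shared sessions and peers are enough to raise the point.
- The hypothesis is set at 12 months, about ten months after the sessions end. The correlation then may differ from that at week 8, and the article gives no information on either.
- Combining 45 completers per arm with undiminished groups of 10 overstates the loss of power. The table therefore uses 7.5.
- A journal article condenses, and an analysis plan that is not shown may add a random effect. This is fair for details such as variance structure and degrees of freedom. It does not remove the point. The article itself names an analysis without a therapy-group term and fixes the sample size with an independent-patient formula. No later plan can model therapy groups unless membership was recorded during delivery.

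**Conclusion.** The concern holds in conditional form. The stated analysis and sample size do not fit a design in which two arms are group-delivered and one is not. The direction of the error is certain for any positive within-group correlation. Its size cannot be taken from the article. Over the assumed range (groups of 10, 7.5 observed, ICC 0.01 to 0.10) it runs from almost negligible to serious, and the comparison with iMBCT is always hit harder than the comparison with placebo-control. What is firm is that no allowance for clustering was made. That the trial's intervals will in fact be too narrow, or that a therapist effect will pass for a programme effect, goes beyond what the article supports.

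**What to change.** 1. Record a therapy-group identifier for every lifestyle and iMBCT patient while the sessions are being delivered.
2. Analyse BDI-II with a partially nested mixed model: a random therapy-group effect in the two group-delivered arms only, placebo-control patients as singletons, residual variance allowed to differ by arm, and small-sample degrees of freedom.
3. Make the multiple imputation reflect therapy group too, so that it matches the analysis model.
4. Restate the power in section 2.8 over a stated range of group size and ICC. The enrolment target of 180 can stay.

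The cost is one data field and a model specification; Stata 16.1 is already listed in section 2.11. Intervals will be somewhat wider. With 60 per arm and groups of 10 there would be only 60/10 = 6 groups per arm, so the group variance will be estimated imprecisely, and this should be acknowledged. The model also cannot separate a therapist effect from a programme effect if one therapist leads all groups in an arm.

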One of the main challenges of Internet-based clinical interventions is the difficulty in establishing an adequate therapeutic bond, an essential component for successful psychological interventions. However, previous studies suggested that online therapies can establish satisfactory therapeutic alliances.^[30]^ Despite the great advances in the online treatment of depression, many aspects of these interventions require further study, such as the efficacy of online multimodal lifestyle programs for patients with TRD.

There is little scientific evidence supporting the benefits of an online adjuvant healthy lifestyle promotion program for patients with TRD, probably because implementation of these interventions is difficult.^[31]^ There is evidence that psychotherapy delivered by telephone or online may be useful for patients with depression, but less information is available regarding the use of Internet-based programs that focus on lifestyle in health emergency situations in which people are required to restrict their mobility and maintain physical distance.^[32,33]^ As far as we are aware, no previous studies have examined the effect of this approach for patients with TRD.

The main objective of this study is to analyze the effectiveness of treatment prescribed by the mental health team, written suggestions for lifestyle changes, and an 8-week lifestyle change promotion program in patients with TRD. There will be 2 control groups: a placebo control group will receive treatment prescribed by the mental health team and written suggestions for lifestyle changes; an active control group will receive treatment prescribed by the mental health team, written suggestions for lifestyle changes, and an 8-week iMBCT program, an intervention that has proven effectiveness in a face-to-face format.^[34,35]^

We hypothesize that patients randomized to the lifestyle intervention group will show significantly greater improvements in clinical measures of depression than patients from the 2 control groups at 12 months.

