### Outcomes measures

2.6

The primary outcome measure will be the severity of depression based on the Beck depression inventory-II (BDI-II). The secondary outcome measures will be the scores from scales that rate global clinical impression, quality of life, comorbidities, social support, mindfulness skills, physical activity, adherence to the Mediterranean diet, severity of insomnia, self-compassion, and acceptance and action.

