### Participant timeline

2.7

We will collect patient data using questionnaires administered at baseline (week-0), immediately after the intervention (week-8), at month-6, and at month-12 (Table 2).

**Table 2 T2:** Timeline for enrolment, allocation, interventions, and assessments.

	Study period				
	
	Enrolment	Intervention	Post-allocation		Close-out
				
Timepoint	−1 wk	0	8 wk	6 mo	12 mo
Enrolment					
Eligibility screen	X				
Informed consent	X				
Allocation		x			
Interventions					
MBCT intervention			x		
Lifestyles intervention			x		
Placebo		x			
Assessments					
Chronic conditions (ICD-10), BDI-II	x				
BDI-II, GCI, EQ-5D-3L			x	x	X
MOS-SS, IPAQ-SF, MEDAS, ISI			x	x	x

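### The stated analysis of variance names no baseline BDI-II covariate although the score is taken before allocation; it is valid, but adjustment would give more power at essentially no cost

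*Protocol article*

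**What the plan says.** Section 2.11 (Statistical analyses) gives one sentence on the comparison of arms: "Analysis of variance will be used to compare the 3 groups at multiple time points". It names no covariate, and neither ANCOVA nor a mixed model appears anywhere in the article. The same section does settle the analysis sets, multiple imputation, a complete-case sensitivity analysis and the software.

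The baseline score precedes allocation. Table 2 in section 2.7 has a row "Chronic conditions (ICD-10), BDI-II" marked at −1 week, with allocation marked at 0. Section 2.9 says "If a participant is eligible, the researcher will administer the baseline questionnaire", and section 2.10 says "After the enrolment visit, each patient will be randomly assigned to the MBCT Intervention, Lifestyles Intervention or Placebo group in a 1:1:1 ratio".

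The Introduction's hypothesis is that the lifestyle arm will show "significantly greater improvements in clinical measures of depression" than both control groups at 12 months. For the sample size, section 2.8 states "we considered a reduction of 6 points or more to indicate a clinically significant benefit", takes an SD of 9.8 from a baseline mean of 24.5, allows for 25% dropout, and concludes: "Accepting an α risk of 0.05 and a β risk of 0.15 in a bilateral contrast, 60 subjects will be required for each group".

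**The concern.** A patient's BDI-II at entry usually predicts part of the later score. Using it as a covariate removes that part of the outcome variance, and an analysis without it leaves the variance in the standard error. The hypothesis concerns improvement, so the starting score is part of the question. The eligibility criteria set no BDI-II limits, so baseline scores may vary widely.

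Precision is at stake, in a trial with little to spare: if dropout reaches the planned maximum, an unadjusted comparison falls somewhat short of the planned 85% power. There is also an ambiguity. The sentence in section 2.11 can mean separate analyses of follow-up scores or a repeated-measures analysis that includes baseline. These estimate the 12-month difference differently and have different power.

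**Working it through.** **Inputs.** From section 2.8: difference 6 points, SD 9.8, two-sided α 0.05, β 0.15, dropout 25%, 60 per arm. The baseline to 12-month correlation r is not in the article, so I assume 0.2 to 0.6. I also assume an SD of 9.8 at both times.

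**The plan's own figure.** Per arm, n = 2 × [9.8 × (1.960 + 1.036) / 6]² = 47.9, so 48. The stated 60 is 48 × 1.25. The raw SD is used, so no gain from baseline adjustment is built in. A 25% loss from 60 leaves 60 × 0.75 = 45 per arm.

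**Unadjusted power** (two-sample t, noncentral t distribution):
- 60 per arm: 91.4%
- 45 per arm: 81.9%, against the planned 85%

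**Alternatives at 45 per arm.**
- Baseline-adjusted: residual SD = 9.8 × √(1 − r²). At r = 0.5 this is 9.8 × 0.866 = 8.49.
- Raw change, which is what the 12-month contrast becomes in a repeated-measures analysis with baseline as a level: SD = 9.8 × √(2(1 − r)). At r = 0.4 this is 9.8 × 1.095 = 10.74.

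| Assumed r | Variance removed (r²) | Adjusted SD | Power, adjusted | Power, raw change | Power, unadjusted |
|---|---|---|---|---|---|
| 0.2 | 4% | 9.60 | 83.4% | 62% | 81.9% |
| 0.3 | 9% | 9.35 | 85.3% | 68% | 81.9% |
| 0.4 | 16% | 8.98 | 88.0% | 75% | 81.9% |
| 0.5 | 25% | 8.49 | 91.3% | 82% | 81.9% |
| 0.6 | 36% | 7.84 | 94.8% | 89% | 81.9% |

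The adjusted analysis has the most power in every row. It reaches 85% at r of about 0.3, and it reaches the 91.4% of 60 unadjusted patients per arm only above r of about 0.5. Raw change does worse than no adjustment below r = 0.5 and equals it at 0.5.

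**Chance imbalance.** The standard error of a baseline difference between two arms of 60 is 9.8 × √(2/60) = 1.79 points. Only r times such a difference is expected to carry over to follow-up: 0.4 × 1.79 = 0.7 points to 0.6 × 1.79 = 1.1 points, which is 12% to 18% of the 6-point target. This is part of the variance in the table, not a further loss.

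**Simplification.** The calculation treats 45 completers per arm as the information available. Multiple imputation using week-8 and month-6 scores could add a little.

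**The case against.** The strongest reply is that a condensed article need not list model terms, that a separate analysis plan may add covariates, and that the sentence never says the analysis is unadjusted. The general rule is sound, and a later plan may well settle the matter. But the article does more than stay silent: it names the method. The point is about that named method, for which a better one is available from data already scheduled.

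A second reply is that "Analysis of variance will be used to compare the 3 groups at multiple time points" may mean a repeated-measures analysis with baseline as one of its time points. That is a fair reading, and it would be wrong to say that baseline is certainly ignored. It does not remove the point, because the resulting change contrast has less power than the adjusted analysis at every r shown.

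A third reply is that the gain rests on an unknown r, and that the shortfall from 85% comes from how dropout was allowed for. Both are true. At r = 0.2 the gain is only 1.5 percentage points (83.4% against 81.9%), and the dropout allowance is a separate matter. The direction of the gain does not depend on either.

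Three stronger readings are tempting, and the document does not support them:
- **That the analysis is biased or invalid.** Randomisation protects it; the issue is efficiency.
- **That chance baseline differences pass in full into the result**, putting 1.8 points at risk. Only the fraction r carries over, and the unadjusted standard error already allows for it.
- **That adjustment makes up for all the power lost to dropout.** This holds only above r of about 0.5.

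**Conclusion.** The point holds as one of efficiency. The article fixes a method that is valid but makes less use of the pre-allocation BDI-II than an adjusted analysis would. Under the planning figures, with 45 completers per arm, adjustment raises power from 81.9% to between 83.4% (r = 0.2) and 94.8% (r = 0.6), with no extra patients. The gain is small at the lower end and material from about r = 0.3, where the planned 85% is restored. These sizes rest on the assumed r, an SD of 9.8 at both times, and dropout at its stated maximum. The ranking of the adjusted analysis above both readings of the stated one holds throughout the range examined.

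**What to change.** In section 2.11, prespecify that the primary estimates are the 12-month BDI-II differences, lifestyle minus each control, with 95% confidence intervals, from an ANCOVA with baseline BDI-II as a covariate. An equivalent mixed model across week 8, month 6 and month 12 with the same covariate would also serve. State that baseline BDI-II is included in the multiple imputation model.

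The cost is a change of wording before the data are analysed. The baseline measurement is already scheduled, and the named packages (SPSS and STATA) can fit either model. Fixing the model in advance also settles which reading of the current sentence is meant and removes a later choice between adjusted and unadjusted results.
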